### Intervention and Control

The intervention group will receive 2 professionally administered FV applications. Applications will occur at baseline (month 0) and at 6 months, using Duraphat (Colgate-Palmolive Company) varnish, which contains 5% sodium fluoride by weight, equivalent to 22,600 parts per million fluoride ions [16,17]. The varnish will be applied to all erupted tooth surfaces by trained dental professionals under standard infection control procedures, including hand hygiene, appropriate personal protective equipment, and the use of single-use disposable materials to prevent cross-contamination, in accordance with Centers for Disease Control and Prevention guidelines for portable dental care [18]. A brief oral examination will be conducted prior to each session to confirm eligibility for varnish application. Prior to application, the teeth will be cleaned with sterile gauze and isolated with cotton rolls for moisture control [19]. The tooth surfaces will then be dried with gauze, followed by the application of 0.40 mL of 5% sodium fluoride varnish [20]. Concurrently, oral health education will be provided to parents and teachers of students. These educational sessions will be delivered during the school visits in which varnish applications occur. Content will include basic oral hygiene practices, the importance of fluoride in caries prevention, dietary advice, and strategies for supporting children with disabilities in maintaining oral health.

The control group will receive standard care, consisting of annual oral health examinations and oral health education. These educational components will be delivered during routine school visits using the same materials and format as in the intervention group, ensuring comparability of educational exposure between groups. However, no FV will be applied in control schools during the study period. The overview of the study is shown in Figure 2.

**Figure 2. F2:**
[figure not shown]
Overview of the study design and timeline for the fluoride varnish intervention in special education schools in Guangdong Province from 2025 to 2026.

### Study Outcomes

The primary outcome of this study is the prevalence of dental caries among students at 12 months following the intervention. Dental caries will be assessed through clinical oral examinations using the decayed, missing, and filled teeth index (DMFT) for permanent and primary dentition, respectively. These examinations will be conducted in accordance with the national standardized child oral health survey protocol used in China. Briefly, trained and calibrated dental professionals will perform tooth-level examinations using disposable dental mirrors and probes under natural or portable lighting. Dental status for both primary and permanent teeth, including caries experience and related conditions, will be recorded. Examinations will take place in a designated room with adequate lighting [21]. Children will be assessed while seated [22], and wheelchair users will remain in their own wheelchairs. Two familiar teachers or school support staff will attend to assist with communication and comfort [23]. A trained dentist will conduct the examination, and a trained nurse will record the number of decayed, missing due to caries, and filled teeth per child. The blank recording form is provided in Figure 3. To minimize measurement bias, examiners conducting the follow-up assessments will be blinded to the school allocation status.

Secondary outcomes include (1) oral hygiene status (eg, presence of plaque and gingivitis), assessed using gingival health indicators and plaque indices; (2) changes in oral health–related knowledge, attitudes, and practices (KAP) among students, parents, and teachers, measured using a structured questionnaire adapted from the Third National Oral Health Survey [24].

Baseline assessments will be conducted prior to intervention implementation, with follow-up occurring 12 months later. Oral examinations will be performed on-site in schools, with each child examined in a standardized manner. KAP questionnaires will be administered to parents and teachers at both baseline and the end of follow-up. All data will be collected using the Wenjuan Star platform (Shanghai Zhongyan Network Technology Co Ltd) or through paper-based questionnaires with double data entry, depending on the logistical feasibility at each study site. Data from paper questionnaires will be manually entered into the electronic system by trained students at the university. Details of the information collected are shown in Table 1. Monitors appointed by the trial sponsor will oversee trial implementation to ensure protocol compliance and data accuracy (Multimedia Appendix 1).

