## Introduction

Oral health is a critical component of general health and quality of life, yet children with disabilities remain an underserved population with significantly elevated risk for oral diseases [1,2]. Studies across multiple settings have consistently shown that students with disabilities experience a higher prevalence and severity of dental caries, gingival inflammation, and oral hygiene problems than their peers without disabilities [3]. This disparity is attributed to a range of factors, including motor or cognitive impairments, reduced self-care abilities, dependence on caregivers, behavioral challenges, and limited access to dental services [3,4]. In China, these challenges are compounded by underdeveloped oral health support systems within special education settings, despite national goals to promote equitable health access for all populations [5].

Fluoride varnish (FV) is widely endorsed as an effective caries-preventive intervention, particularly in children at moderate to high risk [6,7]. Meta-analyses, including multiple Cochrane reviews encompassing more than 200 trials and 80,000 participants, have consistently reported significant reductions in caries incidence, up to 43% in permanent teeth and 37% in primary teeth, with biannual professional FV application [6-9]. Additional studies have demonstrated its efficacy in preventing white spot lesions in adolescents with orthodontic appliances and reducing caries in special-needs populations, such as children with attention-deficit/hyperactivity disorder [10,11]. However, the overall body of evidence remains inconclusive. Some more recent systematic reviews and large-scale trials have shown limited or no significant benefit, particularly in low-risk populations or settings with high background fluoride exposure [7,12]. Furthermore, substantial heterogeneity across studies, limited methodological quality in earlier trials, and uncertainty in comparative effectiveness vs other preventive interventions (eg, sealants) complicate interpretation [9,13]. This conflicting evidence underscores the need for rigorously designed, context-specific evaluations of FV effectiveness, particularly in high-risk, underserved populations, such as children with disabilities in school-based settings.

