### Sample Size

The primary outcome of this study is the prevalence of dental caries at 12 months. On the basis of previous literature in comparable populations, the prevalence of caries among students in special education schools without intervention is estimated at 60% [5,14]. A reduction to 40% in the intervention group is considered clinically and politically meaningful [9,15]. Using a 2-sided α of .05 and a power of 90% (β=.10), the required sample size per group for an individually randomized trial is estimated using the formula:

$$n=\frac{{\left(z_{\alpha /2}+Z_{\beta }\right)}^{2}\times \left(p_{1}(1-p_{1})+p_{2}(1-p_{2})\right)}{{\left(p_{1}-p_{2}\right)}^{2}}$$

where *z*_*α*/2_ is 1.96, *Z*_*β*_ is 1.28, *p*_1_ is 0.60, and *p*_2_ is 0.40. Substituting these values gives a sample size of approximately 126 per group under individual randomization. Additionally, this study uses a stratified cluster RCT design, which requires adjustment for clustering using the design effect. The design effect was calculated as 1+(m–1)×*ρ* where *m*=150 (average cluster size, ie, school size), *ρ* is 0.02 (intracluster correlation coefficient). The resulting design effect was calculated as 3.98, yielding an adjusted sample size of 501 students per group. Allowing for an anticipated 10% dropout rate, the final required sample size is 557 students per group, totaling 1114 participants across all clusters. On the basis of the final required sample size of 557 students per group and an average cluster size of 150 students per school, the required number of clusters was calculated as 557/150=3.71 per group. Therefore, at least 4 schools per group, corresponding to a minimum of 8 clusters in total, are required.

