## Discussion

### Hypothesized Findings

Biannual FV application, integrated with tailored oral health education for parents and teachers, is anticipated to be an effective intervention for caries control, significantly reducing the prevalence of dental caries among students in special education schools in Guangdong Province. We anticipate a significantly lower incidence of new caries and a higher rate of oral hygiene improvement—as measured by plaque and gingival indices—in the intervention group. Furthermore, the intervention is expected to significantly improve parental and teacher health literacy and oral health–related KAP scores. This study integrates professional clinical prevention with school-based education, aiming to generate critical evidence to inform national oral health strategies and policies for children with disabilities in China.

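### The 60% to 40% fall in 12-month caries prevalence behind the stated 90% power is not credible for a DMFT-scored outcome in students enrolled whatever their baseline caries

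*Protocol article*

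**What the plan says.** Under Study Outcomes: "The primary outcome of this study is the prevalence of dental caries among students at 12 months following the intervention". The same section says how caries is measured: "Dental caries will be assessed through clinical oral examinations using the decayed, missing, and filled teeth index (DMFT) for permanent and primary dentition, respectively". It adds that "a trained nurse will record the number of decayed, missing due to caries, and filled teeth per child". Table 1 lists tooth-level codes: A for no caries, B for crown caries, C and D for filled teeth with and without caries, and E for teeth missing through caries. The article does not spell out when a student counts as a case.

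Inclusion and Exclusion Criteria admit enrolled students with consent and do not exclude existing caries. The Abstract gives ages 5 to 22.

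Sample Size says "the prevalence of caries among students in special education schools without intervention is estimated at 60" percent, and continues: "A reduction to 40% in the intervention group is considered clinically and politically meaningful". With 90% power, an ICC of 0.02, 150 students per school and 10% dropout, this leads to 557 students per group.

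The evidence and the hypothesis concern new disease. The Introduction cites "significant reductions in caries incidence, up to 43% in permanent teeth and 37% in primary teeth", and Hypothesized Findings says "We anticipate a significantly lower incidence of new caries". Statistical Analysis plans a mixed-effects logistic model adjusted for, among other covariates, baseline oral health status.

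**The concern.** Varnish is expected to prevent new lesions. Prevalence at 12 months mixes those new lesions with disease present before the first application. A tooth that is filled, or extracted because of caries, still counts towards DMFT, so a student affected at baseline normally remains affected at month 12. Because schools were randomised before varnish was applied, both arms should start at about the same prevalence. The between-arm difference can then come only from students who were caries-free at baseline, and it is limited by how many of them develop caries in one year.

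At stake is the power statement. A null result from a trial described as having 90% power would be read as evidence that varnish does not work in special education schools, when the design could not show a 20-point difference on this outcome. New lesions in students already affected at baseline would also not count.

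**Working it through.** **1. The plan's own figure.** n = (1.96 + 1.28)² × (0.60×0.40 + 0.40×0.60) / 0.20² = 125.97, so 126. Design effect = 1 + 149×0.02 = 3.98. 126 × 3.98 = 501. 501 / 0.90 = 556.7, so 557 per group and 1114 in total. The arithmetic reproduces. The problem is the effect put into it.

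**2. Is 60% to 40% attainable?** Let b be baseline prevalence, i the 12-month incidence in caries-free students and e the relative reduction in incidence. With no reversal of existing DMFT experience:

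- control at 12 months = b + (1 − b)·i
- varnish at 12 months = b + (1 − b)·i·(1 − e)

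*Reading A: 60% is the baseline level.* The varnish arm cannot fall below 60%. To reach 40%, 0.20/0.60 = one third of affected students would have to become caries-free, with no new cases.

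*Reading B: 60% is the control arm's 12-month value.* The difference is (0.60 − b)·e = 0.20, so b = 0.60 − 0.20/e and i = (0.60 − b)/(1 − b).

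| e | b needed | i needed |
|---|---|---|
| 100% | 40% | 33% |
| 43% | 13.5% | 54% |
| 37% | 6% | 57% |

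**3. Power for attainable differences.** From the article: 12 schools split 7:5, about 1100 students, 10% dropout, ICC 0.02. Students analysed per school: 1100/12 × 0.9 = 82.5. Design effect = 1 + 81.5×0.02 = 2.63. Assumed: b = 60%, and i = 10% to 30%, because the documents give no incidence. The cited 43% and 37% are applied at person level as a simplification.

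SE² = 2.63 × [pC(1 − pC)/(5×82.5) + pT(1 − pT)/(7×82.5)]. Power is taken from the non-central t with 10 df and non-centrality (pC − pT)/SE.

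| i | e | Control | Varnish | Difference | Power |
|---|---|---|---|---|---|
| 10% | 37% | 64.0% | 62.5% | 1.5 points | 6% |
| 20% | 43% | 68.0% | 64.6% | 3.4 points | 10% |
| 30% | 43% | 72.0% | 66.8% | 5.2 points | 16% |

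Even complete prevention (e = 100%) gives only 11% at i = 10% and 60% at i = 30%.

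**4. Allowing for the planned baseline adjustment.** If adjustment in effect confines the information to the 40% who are caries-free, there are 0.40 × 82.5 = 33 per school, with design effect 1 + 32×0.02 = 1.64. The comparison is i against i(1 − e). Power is about 15% at i = 10%, e = 37%, and about 55% at i = 30%, e = 43%.

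**5. The increment outcome, any new affected tooth, in all students.** Here i is the share of all control students with at least one new affected tooth, with 82.5 per school and design effect 2.63.

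| i | Power, e = 37% to 43% |
|---|---|
| 10% | 21% to 27% |
| 20% | 40% to 52% |
| 30% | 60% to 74% |
| 40% | 78% to 89% |

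**The case against.** Five points can be made for the plan.

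*The unadjusted power is not that of the planned analysis.* This stands. A reader might infer from 6% to 16% that the trial will almost certainly report no effect. The primary model adjusts for baseline oral health status, and the approximation in step 4 gives 15% to 55%. How close the model comes depends on how that covariate is coded, which the article does not say. Either way power is well short of 90%.

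*The article never calls the outcome cumulative.* This also stands. A reader might infer that prevalence cannot fall by definition, but no person-level case definition is given, and the Table 1 codes would allow one based on untreated decay. That does not rescue the assumption. Under such a definition reversal would come from restorations, which are not part of the intervention described. Shedding of carious primary teeth can lower prevalence under either definition, but it occurs in both arms and is not a varnish effect.

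*A 60% baseline is only one reading.* True, but the other reading needs a combination of baseline and incidence that is equally hard to believe.

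*The 40% may not derive from the cited incidence reductions.* Correct. Sample Size offers it as a meaningful reduction with its own references, so the documents do not support saying that an incidence effect was carried over to prevalence. The point does not need that claim.

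*Changing the outcome is partly a preference and does not cure the power problem.* A reader who looked only at 40% incidence might think the increment outcome nearly restores the stated power. At 10% to 30% it gives 21% to 74%. Keeping prevalence with a restated power is a defensible minimum.

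**Conclusion.** The concern holds. No passage reconciles a 20-point fall in 12-month prevalence with DMFT scoring, unrestricted baseline caries and a preventive treatment, and the assumption fails under either reading of the 60%. The 90% power claim is unsupported, although the sample size arithmetic is correct.

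The size of the shortfall is less certain than its existence. The ranges of about 6% to 16% unadjusted and roughly 15% to 55% with adjustment depend on an assumed 60% baseline, 10% to 30% incidence in caries-free controls, the cited reductions applied per person, an ICC of 0.02 and about 83 students analysed per school. The no-reversal argument depends on a DMFT-based case definition, which the article implies but does not state.

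**What to change.** By a declared amendment before any month-12 data are analysed:

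- State the person-level case definition.
- Make the primary outcome the 12-month caries increment in all students, taken from the tooth-level codes recorded at both examinations: at least one tooth sound (A) or unerupted at baseline and coded B, C, D or E at month 12. Shed primary teeth do not count as reversals.
- Keep prevalence at 12 months as a secondary outcome.
- Replace the 60% to 40% assumption with an increment assumption, and restate power for the 12 enrolled schools over a range of incidences, as in step 5.

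If prevalence is kept as primary, the minimum is to withdraw the 90% claim and restate power for the baseline-adjusted analysis under an attainable difference.

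The change needs no new visits, students or measurements, and the article says analysis has not started. Its cost is a declared change of primary outcome in an open-label trial after baseline and the first varnish application, and a less favourable stated power.

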**Figure 3. F3:**
[figure not shown]
Blank recording form for oral examination.

**Table 1. T1:** Baseline information collected via a questionnaire and oral health examination.

Domains and variables	Units and categories
Demographics	
Sex	Male; female
Age	Years
Ethnicity	Han; other
Height	Centimeters
Weight	Kilograms
School	School name
Grade	Primary; middle; high
Class	Class name or number
Socioeconomic information	
Parent’s education level	Junior high; high school; college; postgraduate
Parent’s occupation	Government; private; other
Perceived dental cost burden	Very cheap to very expensive
Caregiving context	
Relationship to child	Father; mother; grandparent; other
Primary caregiver	Parent; relative; nanny; other
Boarding status	Yes; no
Dietary habits	
Sweet food or drink preferences	Yes; No
Use of sweets as rewards	Never; sometimes; often; unknown
Night-time snack intake	Never; sometimes; often; unknown
Daily sugar intake frequency	≥3 times/day: yes; no; unknown
Tooth brushing start age	<1 year; 1-2 years; etc
Brushing frequency	≥3 times/d; twice daily; once daily; irregular
Fluoride toothpaste use	Yes; no; unknown
Brushing assistance	Self; helped
Oral hygiene methods	Toothbrush, floss, rinse, etc.
Dental treatment history	
Toothache in past 12 months	Never; sometimes; often; unknown
Dental visits	Yes; no
Time since last visit	<6 months, 6-12 months, or >12 months
Visit reason	Check-up; treatment; prevention
Dental cooperation level	+ + fully cooperative; + cooperative; – + mixed response; – negative; – – completely uncooperative
General anesthesia experience	Yes; no
Oral health knowledge and attitudes	
Oral health knowledge	Correct; incorrect; don’t know
Attitudes toward prevention	Agree; disagree; don’t know
Misconceptions about oral care	True; false; don’t know
Parental burden and psychosocial status	
Time burden	Never to always (5-point scale)
Emotional stress	Never to always (5-point scale)
Social impact	Never to always (5-point scale)
Future concern for child	Never to always (5-point scale)
Disability profile	
Disability type	Vision; hearing; speech; intellectual; autism; physical; multiple; other
Disability severity	Mild; moderate; severe; very severe; unknown
Age at diagnosis	Years
Diagnosing hospital	Hospital name
Medication or comorbidities	Yes; no (specify)
Gastrointestinal and behavioral symptoms	
Stool frequency	Times: week
Stool consistency	Normal; loose; watery
Bloating	Days/week
Abdominal pain	Days/week
Sleep disturbances	Times/week
Feeding behaviors	
Selective eating	Never to always (5-point scale)
Texture or color sensitivity	Never to always (5-point scale)
Food rituals	Never to always (5-point scale)
Disruptive mealtime behaviors	Never to always (5-point scale)
Food refusal behaviors	Never to always (5-point scale)
Oral health examination variables	
Caries type (eg, no caries, crown caries, filled with/without caries), primary vs permanent teeth	A: no caries; B: crown caries; C: filled with caries; D: filled without caries; E: missing due to caries; X: missing for other reasons
Tooth trauma type	Trauma types: enamel crack, enamel fracture, crown-dentine fracture, pulp exposure, avulsion, other
Crown discoloration	+; –
Tooth mobility	+; –
Presence of fistula	+; –
Tooth eruption stage	One-third; two-thirds; full
Presence of supernumerary teeth	Yes; no
Presence of fissure sealant	Yes; no
Presence and type of dental fillings	Yes; no (type noted)
Missing teeth due to caries or other reasons	Yes; no (reason noted)
Exposure of pulp in traumatic crown fractures	Yes; no
Periodontal condition measured using plaque index and gingival index	Clinical description

### Data Collection

Data will be collected at baseline and at the 12-month follow-up according to prespecified study-specific procedures. Trained dental professionals will perform oral examinations. They will use the DMFT index [25]. Examiners also record periodontal status, including plaque index and gingival index, as well as tooth eruption and trauma [26]. At the same time, parents and teachers will complete structured KAP questionnaires. All paper records will be double-entered to reduce errors. Monitors will oversee the process to ensure protocol adherence and data accuracy.

### Statistical Analysis

All data will be entered into a centralized electronic data capture system with built-in logic checks to ensure completeness and internal consistency. Statistical analyses will be conducted using Stata (version 18.0; StataCorp LLC). Descriptive statistics will first be generated to summarize baseline characteristics of participants in both intervention and control groups, including means, SDs, proportions, and frequency distributions.

Comparative analyses between groups will be conducted on an intention-to-treat basis. Participants will be analyzed according to their randomized group, regardless of receipt of FV. For descriptive and unadjusted comparisons between groups, chi-square tests will be used for categorical outcomes (eg, caries prevalence). For continuous variables, independent-samples *t* tests will be used for normally distributed data, and nonparametric tests (eg, Mann-Whitney *U* test) will be applied for skewed distributions. Paired comparisons (eg, baseline vs 12-month follow-up) within groups will use paired *t* tests or Wilcoxon signed-rank tests as appropriate.

To evaluate the effectiveness of the intervention while accounting for potential confounders and cluster randomization in the primary analysis, mixed-effects logistic regression will be used for binary outcomes, such as caries presence, and mixed-effects linear regression for continuous outcomes, such as the number of decayed teeth [27]. Models will adjust for relevant covariates, including age, sex, socioeconomic status, and baseline oral health status. Multiple imputation with chained equations will be applied to handle missing covariate data. Cluster effects will be accounted for using robust SEs or multilevel modeling, as appropriate. Effect estimates will be presented as adjusted odds ratios or mean differences with 95% CIs. All hypothesis testing will be 2-sided, with a significance level set at *P*<.05. Sensitivity analyses, including subgroup analyses by economic region, will be conducted to assess the robustness of the findings.

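### The unadjusted between-arm tests, including the one for caries prevalence, ignore school clustering: about 23% to 24% type I error at the enrolled size (ICC 0.02); the primary mixed-effects analysis is not affected

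*Protocol article*

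**What the plan says.** The Statistical Analysis section of the protocol article has two layers of between-arm comparison.

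- **Unadjusted layer.** For categorical outcomes: "For descriptive and unadjusted comparisons between groups, chi-square tests will be used for categorical outcomes (eg, caries prevalence". For continuous ones: "For continuous variables, independent-samples *t* tests will be used for normally distributed data". Skewed data get a rank-based test instead, with Mann-Whitney as the example. No allowance for clustering is stated for any of these. Paired t or Wilcoxon signed-rank tests are added for change within each arm.
- **Primary layer.** The effectiveness analysis is described as "accounting for potential confounders and cluster randomization in the primary analysis, mixed-effects logistic regression will be used for binary outcomes", with mixed-effects linear regression for continuous outcomes. The text then adds: "Cluster effects will be accounted for using robust SEs or multilevel modeling, as appropriate".

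One rule covers both layers: "All hypothesis testing will be 2-sided, with a significance level set at *P*<.05".

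The Sample Size section takes clustering seriously. With 150 students per school and an ICC of 0.02: "The resulting design effect was calculated as 3.98". The section on stratification and randomisation confirms that the school is the unit of allocation, stratified by city, with 7 intervention and 5 control schools.

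**The concern.** The chi-square, t and Mann-Whitney tests are valid when observations are independent. Students in the same school are not, and the plan says so when it roughly quadruples its sample size for clustering. Caries prevalence, the example named for the chi-square test, is the primary outcome. Because the 5% two-sided rule applies to all hypothesis testing, these comparisons are tests and not only descriptive tables.

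At stake is an unadjusted P value for the primary outcome that is much too small. If reported, it would stand beside the clustered result and could disagree with it for no reason other than the neglected clustering. The abstract also defines the primary outcome as a difference in prevalence, while the binary model reports an odds ratio, so a reader could easily turn to the simple comparison of two percentages.

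The within-arm paired tests raise a separate and milder issue: a change within one arm does not compare the randomised arms, whatever its P value.

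**Working it through.** **Inputs from the protocol article**

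- Sample Size: two-sided alpha 0.05 (z = 1.96), power 90% (z = 1.28), prevalences 0.60 and 0.40, ICC 0.02, 150 students per school, dropout 10%.
- Randomisation section and Results: 12 schools (7 and 5), more than 1100 students recruited.

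**Step 1: the plan's own figures**

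- Individual randomisation: (1.96 + 1.28)² × (0.24 + 0.24) / 0.20² = 125.97, so 126 per group.
- Design effect: 1 + (150 − 1) × 0.02 = 3.98.
- 126 × 3.98 = 501.5, given as 501. Then 501 / 0.9 = 556.7, so 557 per group and 1114 in total.

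All of these reproduce.

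**Step 2: cluster size as enrolled**

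- As recruited: 1100 / 12 = 91.7 per school.
- After 10% dropout: 990 / 12 = 82.5 per school.

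**Step 3: type I error of a test that ignores clustering**

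Under no effect, the naive z statistic has variance of about DE = 1 + (m − 1) × ICC instead of 1. A nominal 5% test therefore rejects with probability 2 × (1 − Φ(1.96 / √DE)).

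| Students per school (m) | DE | √DE | Type I error |
|---|---|---|---|
| 82.5 (enrolled, after dropout) | 2.63 | 1.62 | 22.7% |
| 91.7 (enrolled) | 2.81 | 1.68 | 24.3% |
| 150 (planned) | 3.98 | 1.99 | 32.6% |

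The √DE column is the factor by which the naive standard error is too small.

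**Step 4: check by simulation under no effect, ICC 0.02, equal school sizes**

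| Schools, m | Chi-square | t test | Mann-Whitney |
|---|---|---|---|
| 7 v 5, m = 83 | 22.9% | 22.5% | 21.5% |
| 7 v 5, m = 92 | 24.6% | 25.1% | 24.3% |
| 4 v 4, m = 150 | 32.8% | 32.9% | 32.3% |

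The chi-square column uses beta-binomial data with prevalence 0.60. The other two use a normal random intercept with the same ICC. That ICC is an assumption for continuous outcomes, because the document gives the value only for caries prevalence.

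**Step 5: sensitivity to the ICC**

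The values 0.01 and 0.05 are assumptions and do not come from the document. At the enrolled size (82.5 to 91.7 per school), ICC 0.01 gives 14.6% to 15.6% and ICC 0.05 gives 38.4% to 40.5%.

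The direction of two further influences is known. Unequal school sizes raise the error: with about 83 per school and an assumed coefficient of variation of 0.6, simulation gave 26.1% against 23.1% for equal sizes. Between-school variation explained by city lowers it, because allocation was stratified by city.

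**The case against.** The strongest defence is that the plan does not rest its conclusion on these tests. It confines them to descriptive and unadjusted use and gives the primary analysis to mixed-effects models that account for school randomisation. **This stands.** A reader might infer that the trial's main test carries a false-positive rate of 23% to 33%. The document does not support that: the inflation belongs to the unadjusted P values only.

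Further objections:

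- *The sentence on cluster effects may cover everything.* It follows the regression models and offers robust standard errors or multilevel modelling. The standard tests named in the preceding paragraph use neither, so this does not rescue them.
- *A fuller analysis plan may deal with it.* The point is not an omission. The article names specific tests that do not suit the design.
- *The 33% figure overstates the case.* It belongs to the planned 150 students per school. For the trial as enrolled, 23% to 24% is the relevant figure.
- *Nothing says that the unadjusted P values will be published as the result.* Correct. The stated presentation rule is adjusted odds ratios or mean differences with confidence intervals. Misuse of the unadjusted P value is a risk, not something the plan announces.
- *The within-arm tests.* A reader might carry the same inflation over to the paired tests. That is not supported: a stable school effect cancels in a paired difference, and no calculation shows a comparable error. The only objection made here is that they do not compare the arms.

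**Conclusion.** The point holds for the unadjusted between-arm tests. As written, they do not match the unit of randomisation or the clustering that the sample size calculation assumes. For caries prevalence at ICC 0.02, the actual error of a nominal 5% chi-square test is about 23% to 24% at the enrolled size and about 33% at the planned school size. This rests on equal school sizes and no gain from city stratification. A similar inflation for continuous outcomes is conditional on a similar ICC.

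The primary mixed-effects analysis and its error rate lie outside this finding. It should be corrected because it concerns the primary outcome variable and is easily put right, not because it undermines the trial's main conclusion.

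**What to change.** In the Statistical Analysis section, do one of the following for between-arm comparisons:

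1. Present unadjusted results as numbers, percentages, means and SDs by arm, without P values.
2. Replace the chi-square, t and Mann-Whitney tests with versions that respect clustering. One choice is the planned mixed-effects model without covariates. Another is a test on the 12 school proportions or means, stratified by city. The school-level test is a different method from the primary model and should be labelled so.

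Report change from baseline to 12 months within each arm descriptively, without tests. The baseline table needs no change, since the plan already summarises it descriptively and names no baseline test.

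The cost is a change of wording and larger unadjusted P values. Sample, data collection and the primary model stay as they are, and the article states that analysis has not yet begun.
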